# Awareness with paralysis and symptoms of post-traumatic stress disorder among mechanically ventilated emergency department survivors (ED-AWARENESS-2 Trial): study protocol for a pragmatic, multicenter, stepped wedge cluster randomized trial

**DOI:** 10.1186/s13063-023-07764-5

**Published:** 2023-11-25

**Keywords:** Emergency medicine, Awareness with paralysis, Sedation, Post-traumatic stress disorder, Mechanical ventilation, Critical care

## Abstract

**Background:**

Awareness with paralysis (AWP) is memory recall during neuromuscular blockade (NMB) and can cause significant psychological harm. Decades of effort and rigorous trials have been conducted to prevent AWP in the operating room, where prevalence is 0.1–0.2%. By contrast, AWP in mechanically ventilated emergency department (ED) patients is common, with estimated prevalence of 3.3–7.4% among survivors given NMB. Longer-acting NMB use is a critical risk for AWP, and we have shown an association between ED rocuronium use and increased AWP prevalence. As NMB are given to more than 90% of ED patients during tracheal intubation, this trial provides a platform to test an intervention aimed at reducing AWP. The overall objective is to test the hypothesis that limiting ED rocuronium exposure will significantly reduce the proportion of patients experiencing AWP.

**Methods:**

This is a pragmatic, stepped wedge cluster randomized trial conducted in five academic EDs, and will enroll 3090 patients. Per the design, all sites begin in a control phase, under observational conditions. At 6-month intervals, sites sequentially enter a 2-month transition phase, during which we will implement the multifaceted intervention, which will rely on use of nudges and defaults to change clinician decisions regarding ED NMB use. During the intervention phase, succinylcholine will be the default NMB over rocuronium. The primary outcome is AWP, assessed with the modified Brice questionnaire, adjudicated by three independent, blinded experts. The secondary outcome is the proportion of patients developing clinically significant symptoms of post-traumatic stress disorder at 30 and 180 days after hospital discharge. We will also assess for symptoms of depression and anxiety, and health-related quality of life. A generalized linear model, adjusted for time and cluster interactions, will be used to compare AWP in control versus intervention phases, analyzed by intention-to-treat.

**Discussion:**

The ED-AWARENESS-2 Trial will be the first ED-based trial aimed at preventing AWP, a critical threat to patient safety. Results could shape clinical use of NMB in the ED and prevent more than 10,000 annual cases of AWP related to ED care.

**Trial registration:**

ClinicalTrials.gov identifier NCT05534243. Registered 06, September 2022.

**Supplementary Information:**

The online version contains supplementary material available at 10.1186/s13063-023-07764-5.

## Background

Awareness with paralysis (AWP) is explicit memory recall during neuromuscular blockade (NMB) [1–3]. It is crippling and can cause catastrophic psychological harm including post-traumatic stress disorder (PTSD), depression, anxiety, complex phobias, and lead to suicide [3–9]. Decades of rigorous investigations on hundreds of thousands of patients have been completed with the goal to prevent AWP in the operating room, where prevalence is approximately 0.1–0.2% [3, 10].

By contrast, comparatively little investigation into AWP has occurred among emergency department (ED) patients, where mechanical ventilation is required for almost 400,000 patients annually in the USA [11]. Important risk factors for AWP identified in operating room patients include (1) use of longer-acting NMB; (2) lack of sedation depth monitoring; (3) total intravenous (versus inhaled) anesthesia; and (4) under dosing of anesthesia [1–3, 10]. Clinical data suggests that ED sedation practices place patients at high risk for AWP (Fig. 1). These practices include a lack of any analgesia and sedation for 20–45% of ED patients after intubation, with up to 33% of patients with no sedation depth assessment while mechanically ventilated in the ED [12, 13]. In addition, approximately 90% of patients are given NMB to facilitate tracheal intubation in the ED, with an increasing use of longer-acting NMB such as rocuronium (versus succinylcholine) [14]. Since these patients cannot move, nor relay pain or fear, they commonly receive lower doses of sedation, and in delayed fashion, with up to 25% receiving sedation after a delay of ≥ 50 min [13–16]. Importantly, high variability exists between sites, as the ED-SED Study demonstrated a wide range of (1) no sedation (site ranges, 5.9–52.6%); (2) post-intubation NMB use (0–27.3%); and (3) sedation monitoring (0–100%) [17]. Similarly, in a secondary analysis of the LOTUS-FRUIT study, 26% of ED patients were given no sedation, and 70% had no sedation depth assessed (site ranges, 0–100%) [18].

**Fig. 1 Fig1:**
[figure not shown]
Important risk factors for awareness with paralysis include sedation under dosing, neuromuscular blocker use, and a lack of protocolled monitoring of sedation depth. Every major risk factor for awareness with paralysis commonly occurs in the emergency department

The data cited above provided our research group with the preliminary data to justify further study of AWP among mechanically ventilated ED patients. The ED-AWARENESS Study was a single-center, prospective cohort study which consecutively enrolled 383 mechanically ventilated ED patients over a 12-month period at a large academic medical center [19, 20]. Among survivors given NMB in the ED, the proportion of patients experiencing AWP was 3.3% (10/306; 95% CI, 1.6–5.9%) [19]. In an a priori secondary analysis of the multicenter ED-SED Pilot Trial, we demonstrated that 4.1% (13/314; 95% CI, 2.2–7.0%) of survivors that were given a NMB in the ED experienced AWP [21–23]. Finally, in a single-center prospective cohort conducted at Hennepin County Medical Center (an enrolling site for the current trial), the proportion of patients experiencing an AWP event was 7.4% (66/886; 95% CI, 5.8–9.4%) [24]. Taken as a whole, these data justify a clinical trial aimed at prevention of AWP among mechanically ventilated ED patients and strongly suggest the ED could be a high-yield arena in which to improve patient-centered clinical outcomes.

Psychological trauma and PTSD are a significant burden among the critically ill. PTSD is the development of significant distress or social impairment in someone directly or indirectly exposed to death, threated death, injury, or violence. Critical illness is psychologically traumatic, and 25–35% of survivors experience PTSD [25–27]. These survivors have worse quality of life, greater frequency of pain and substance abuse, increased healthcare cost, and threefold greater risk of death [28–33].

However, similar to AWP, there is a significant knowledge gap with respect to critically ill, mechanically ventilated ED patients. Prior ED-based PTSD work has largely focused on traumatic injury or specifically excluded mechanically ventilated patients [34–37]. In a cohort study of 99 ED patients, our team demonstrated clinically significant PTSD symptoms in 31% of patients with acute respiratory failure, but only 9 patients (9.1%) were mechanically ventilated [38]. Therefore, the burden of PTSD in this cohort is unknown, and the ED could be an optimal target for improving mental health outcomes for several reasons. Critical illness-related mental health disorders are linked to exposures during care, and early frightful memories during illness are linked to higher PTSD prevalence [1, 26]. In addition, delays in care for PTSD are common and linked to refractory symptoms [6, 39–41]. This evidence suggests the early period of critical illness opens a window to reduce psychological morbidity in survivors. The ED-AWARNESS-2 Trial will inform creation of interventions to be used during (not after) an event to mitigate symptom development, and it will use the ED as a target in which to improve outcomes during the “golden hours” (Fig. 2) [34, 42].

**Fig. 2 Fig2:**

Example novel paradigm and hypothesized causal pathway for improving patient-centered outcomes. It is possible that by addressing the early period of critical illness in the emergency department, modifiable targets (increasing provider compassion, decreased patient-perceived threat, preventing awareness with paralysis) can be used to improve patient-centered clinical outcomes

There is significant rationale to target rocuronium use in the ED as a means to prevent AWP. In the ED-AWARENESS Study and ED-SED Pilot Trial, 19/23 (92.6%) AWP patients received rocuronium [19, 23]. In multivariable analysis, rocuronium was independently associated with AWP (adjusted odds ratio, 6.05; 95% CI, 1.46–17.56) [19, 23]. Importantly, AWP was not associated with other sedation-related variables, including (1) sedation monitoring; (2) analgesics, sedatives; or (3) sedation depth. This confirms that a proposal to target ED-based rocuronium may have the greatest chance to improve safety and prevent AWP. This is critical as data from the National Emergency Airway Registry (*n* = 17,583) show rocuronium use was 5% for intubations in 2002, yet up to ~ 45% by 2012 [14]. Use was up to 49% in our ED SED Study, and 60% in the ED-SED Pilot Trial [17, 21]. This indicates that AWP is likely a growing health problem. Contrary to a 5-min duration of succinylcholine (the historical default NMB), rocuronium can paralyze for up to 150 min, greatly increasing AWP risk. In addition, in clinical trials comparing rocuronium versus succinylcholine, with respect to intubating conditions, data has either favored succinylcholine or shown no difference in outcomes [43–45]. However, other preliminary work from our research team did not show an association between rocuronium and AWP risk, but rather pre-intubation mental status [24]. This suggests equipoise in the data and further confirms the need for this large-scale clinical trial.

Our objective is to conduct a pragmatic clinical trial aimed at limiting rocuronium exposure in order to reduce the proportion of mechanically ventilated ED patients experiencing AWP. We hypothesize that limiting rocuronium exposure in the ED, using succinylcholine as the default NMB of choice, will significantly reduce the proportion of patients experiencing AWP.

## Methods

### Trial design

This is a multicenter, pragmatic, stepped wedge cluster randomized superiority trial enrolling at five academic sites over an approximately 3.5-year period, divided into six time periods of 6 months each. A schematic of the trial design appears in Fig. 3. Prior to the trial, each site (one site equals one cluster) was randomly allocated to their position within the design. One cluster will cross to the intervention period, at which point succinylcholine will become the default NMB in the ED, every 6 months (i.e., step duration) from the 2nd to the 6th time period. Cluster order will be determined by computer-based randomization, conducted and generated by the trial statistician (YY), and concealed from each site. To begin, each site will be exposed to control conditions; by the end of the trial, each site will be exposed to the intervention. Enrollment began in June of 2023 and we anticipate recruitment of the total sample size to be completed by September of 2026.

**Fig. 3 Fig3:**
[figure not shown]
Stepped wedge cluster randomized trial where clusters cross to intervention every 6 months (step duration), with a preceding 2-month transition to implement the intervention

A stepped wedge cluster randomized design was chosen for several reasons. It is a robust approach to test quality improvement interventions, such as that in the ED-AWARENESS-2 Trial, and is a rigorous way to study interventions during routine implementation [46, 47]. In addition, randomization of individual patients would be logistically infeasible and yield a small and very selective study population, undermining external validity. Stepped wedge designs are naturalistic because implementation can proceed much as it would without the trial and are also rigorous because they provide randomized evidence of effectiveness [47]. The design also allows between- and within-group comparisons, enhancing statistical power [47–49]. Finally, a stepped wedge study is ideal when evidence already exists, yet there is suboptimal uptake; based on years of operating room research and our preliminary data, we know an effective way to prevent AWP is to limit use of longer-acting NMB, such as rocuronium [3, 19, 23]. The increase in rocuronium use in the ED over the past several years has occurred without any robust randomized evaluation of patient-centered outcomes, as outcomes have typically centered around intubation success rate [14]. The unintended consequence is an incidence of AWP that threatens patient safety. The stepped wedge design provides a means to conduct the first patient-centered, randomized evaluation on this topic and optimizes enrollment due to potential benefits of the intervention while the trial is ongoing.

### Study setting and population

This trial will target mechanically ventilated adult patients in the ED of five academic medical centers. Inclusion criteria are (1) mechanical ventilation via an endotracheal tube; (2) age ≥ 18 years; and (3) treatment with a NMB in the ED (for tracheal intubation or in the post-intubation phase of care). Exclusion criteria are (1) acute or chronic neurologic injury with deficit that prevents assessment of AWP (i.e., stroke, intracranial hemorrhage, traumatic brain injury, cardiac arrest, advanced dementia); (2) death before extubation; and (3) transfer to another hospital from the ED.

Patients will be recruited from the ED at five academic medical centers in the USA: (1) Cooper Medical School of Rowan University, Camden, NJ; (2) University of Iowa, Iowa City, IA; (3) Hennepin County Medical Center, Minneapolis, MN; (4) Barnes-Jewish Hospital/Washington University School of Medicine, St. Louis MO; and (5) Harborview Medical Center, Seattle, WA. Washington University will serve as the Clinical Coordinating Center (CCC) for the trial. The CCC is composed of the overall trial PI, research coordinators, and grants management team, and is responsible for the administration and management of the trial. Mechanically ventilated patients in the ED reflect the composition of the demographics at each of the sites in this study. Based on our preliminary data, we project that the enrollment of women will be approximately 45% and the enrollment of minorities will be approximately 35% Black or African-American, 10% Asian, and 10% Hispanic. We will not exclude any subjects based on gender, race, or ethnicity. We therefore expect that the study findings will hold external validity.

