### Screening and study initiation

This study will identify those patients who present to the ED and require mechanical ventilation. Each site has a system in place for real-time alerts (24 h/day) when mechanical ventilation is used in the ED, and has validated its notification system from the ED to ensure the population of potentially eligible patients will be consecutive mechanically ventilated patients presenting to the ED. All patients that satisfy inclusion and exclusion criteria will be enrolled.

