### Data

Patient-level data will be easily accessible from the electronic medical record. The following baseline characteristics will be collected: age, gender, race, weight, height, pre-existing comorbid conditions, vital signs at presentation, and pertinent laboratory variables. Pre-intubation mental status, drugs used to facilitate intubation, and ventilator settings in the ED will be collected. After the initiation of mechanical ventilation in the ED, all medications related to analgesia and sedation in the ED will be collected. Sedation depth in the ED will be recorded by bedside nurses, using validated sedation depth scales, such as RASS or the sedation-agitation scale (SAS), per existing protocols [70].

The following in-hospital data will be collected: duration of ventilation, agents used for analgesia and sedation during the first 24 h of ICU admission, depth of sedation during the first 7 days after admission, lengths of stay in the ICU and hospital, discharge location, and mortality status (Table 1).

**Table 1 Tab1:** Schedule of screening, data collection, and outcomes assessments for the ED-AWARENESS-2 Trial

Measurement/event	ED	Extubation	^a^1	2	3	4	5	6	7	MV^b^	HOSP D/C	Day 30	Day 180
Inclusion criteria	X												
Exclusion criteria		X											
Demographics, baseline data	X												
Laboratory values	X												
Blood gas values	X		X										
ED procedures and care	X												
Intubation meds and location	X												
Safety events (i.e., intubation success, unplanned extubation, cardiac arrhythmia, allergy, MH)	X												
Ventilator settings/data	X												
Sedation depth (RASS, SAS), documented by bedside nurse	X		X	X	X	X	X	X	X				
Medications for sedation, analgesia, NMB	X		X										
Delirium assessment/CAM-ICU			X	X	X	X	X	X	X				
Assessment of AWP		X											
Ventilator duration										X	X		
Length of stay (hospital and ICU)											X		
Discharge location											X		
Mortality status											X		
Mental health and QOL assessments												X	X

*ED* emergency department; *MV* mechanical ventilation; *MH* malignant hyperthermia; *RASS* Richmond Agitation-Sedation Scale; *SAS* Sedation-Agitation Scale; *NMB* neuromuscular blockade; *CAM* confusion assessment method; *ICU* intensive care unit; *QOL* quality of life

^a^The numbers 1–7 refer to hospital days, with hospital day 1 referring to the first day after admission from the ED

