### Safety monitoring

A data and safety monitoring board (DSMB), independent of the research team and sponsor, will be used to monitor the data. The DSMB will assess safety and efficacy of trial procedures and monitor the overall conduct of the trial. The DSMB also will review adverse event data, other safety data, quality and completeness of data, protocol adherence data, and enrollment data at each meeting to ensure proper trial conduct and continued feasibility of answering the research questions. Meetings between the research team and the DSMB will occur before the study begins, after 25% of the total sample size is accrued each time, and upon trial completion.

The intervention is designed to enhance patient safety by quality improvement related to the selection of neuromuscular blockers by clinicians. Consequently, we aim to see an increase in succinylcholine use during the intervention phase of the trial, which is congruent to clinical practice for more than 40 years and consistent with recommendations for preventing awareness with paralysis. There is over a decade of research on tens of thousands of patients showing equivalent intubation success rates between succinylcholine and rocuronium. In addition, intubation success rate in the ED approaches 100% [14, 54]. We therefore, do not expect to see any difference in intubation success rate between the control and intervention phases, but will track and report this measure. Given the typically small and transient increase in serum potassium of ~ 0.5 to 1 mEq/L known to occur with succinylcholine, there is the potential for an increase in cardiac arrhythmias related to hyperkalemia to occur in the intervention phase. The overall incidence of cardiac dysrhythmia in the peri-intubation period in the ED is approximately 0.7% with no difference between succinylcholine and rocuronium. We therefore do not expect to see any difference in this adverse event between the control and intervention phases, but will track and report this measure [14]. Other very rare adverse events associated with succinylcholine include malignant hyperthermia (incidence ~ 0.009%) and allergic reaction to succinylcholine (incidence 0.01%) [73, 74]. Both of these adverse events are quite unlikely to occur, but will be tracked and reported. Unexpected events will be reported by the site principle investigators to the CCC as detected.

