### Proposed statistical methods

Patient characteristics will be reported using descriptive statistics and frequency distributions. Continuous variables will be compared using independent samples *t*-test or Mann–Whitney *U* test, and categorical variables will be compared using chi-square test or Fisher’s exact test.

AWP will be calculated as proportion (with 95% confidence intervals [CI]) of patients with possible or definite events, as done before [19, 20, 57]. Adjudicator agreement will be assessed, per prior approach, with two-way, random effects, intraclass correlation coefficient for absolute agreement according to 0 = no awareness, 1 = possible awareness, and 2 = definite awareness. All analyses will be intention to treat, such that all patients will be evaluated, regardless of clinician adherence during the intervention phase. The unit of randomization will be the ED, and the unit of analysis will be the patient. The primary analysis will compare the proportion of patients with AWP in the control phase versus the intervention phase. To estimate the intervention effect, mixed effects models and generalized estimating equations (GEE) are most commonly used in stepped wedge designs. However, due to the smaller number of clusters (*n* = 5), it is more appropriate to use a generalized linear model, with cluster included as a fixed effect (i.e., a logistic regression model for binary outcome data with each of five sites as fixed effect) [75–78]. We will first fit a basic model, in which the intervention effect is estimated, adjusting for secular trends (i.e., time effect). We will then extend the basic model by incorporating and testing appropriate interaction terms to test the nature of the intervention effect. Examples include (1) an intervention-by-cluster interaction for heterogeneity of the intervention effect across clusters; and (2) an intervention-by-time for heterogeneity of the intervention effect across time. A possible delayed intervention effect will be tested by changing the intervention indicator (i.e., 0 or 1) into some fractions between 0 and 1, aligned with the time from switching from control to intervention. Unadjusted analyses will also be reported.

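### Exclusions applied at extubation take fatal or disabling events out of the enrolled set, so a by-phase safety comparison in enrolled patients would miss the gravest form of the named harm

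*Protocol article*

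**What the plan says.** Study setting and population admits ventilated adults given an NMB in the ED. It then excludes "acute or chronic neurologic injury with deficit that prevents assessment of AWP (i.e., stroke, intracranial hemorrhage, traumatic brain injury, cardiac arrest, advanced dementia" and, as further criteria, "2) death before extubation; and (3) transfer to another hospital from the ED". In Table 1 (Data section) the inclusion row is marked in the ED column, but the row "Exclusion criteria" is marked in the extubation column. Screening and study initiation adds: "All patients that satisfy inclusion and exclusion criteria will be enrolled".

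Safety monitoring states that "there is the potential for an increase in cardiac arrhythmias related to hyperkalemia to occur in the intervention phase". It quotes a background dysrhythmia rate of about 0.7%, expects no difference between phases, and undertakes to track and report the measure. Table 1 places "Safety events (i.e., intubation success, unplanned extubation, cardiac arrhythmia, allergy, MH" in the ED column and mortality status only at hospital discharge. The same section limits adjudication of adverse events to sites that have already transitioned, and it sets no formal stopping rules.

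Proposed statistical methods says: "All analyses will be intention to treat, such that all patients will be evaluated, regardless of clinician adherence during the intervention phase".

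**The concern.** Two of the exclusions can be consequences of the exposure under study. A patient who has a fatal arrhythmia after the NMB dies before extubation. A patient who arrests and is left with a deficit that rules out interview meets the neurologic criterion. Read as written, the enrollment rule removes both, in either phase. A safety comparison in enrolled patients is then conditioned on having survived the harm in an assessable state.

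What is at stake is mainly the safety conclusion. The article expects no difference in arrhythmia and will report on it. A finding of no difference among survivors to extubation would say little about fatal events, yet it could be read as reassurance about them. The data and safety monitoring board (DSMB) works without formal stopping rules and meets at each 25% of accrual. If accrual counts only enrolled patients, its denominator has the same restriction.

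**Working it through.** **1. Order of events under the article's rules**

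| Event after NMB in the ED | Enrolled? | Seen in a comparison of enrolled patients? |
|---|---|---|
| Non-fatal arrhythmia, extubated, assessable | Yes | Yes |
| Cardiac arrest, recovered, assessable | Yes | Yes |
| Cardiac arrest, deficit prevents AWP assessment | No | No |
| Death before extubation | No | No |
| Death after extubation | Yes | Yes, under mortality status |

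**2. The plan's own figure.** Inputs from Sample size justification: 3.3% versus 0.6%, ICC ρ = 0.001, I = 5 sites, T = 6 periods, α = 0.05 (two-sided assumed), N = 3090. One site crosses per step, so U = 15, W = 55, V = 55, with m = 3090/30 = 103 per site-period.

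The Hussey-Hughes variance is I·s²(s² + Tτ²) / [(IU − W)s² + (U² + ITU − TW − IV)τ²], where s² = v/m and τ² = vρ/(1 − ρ). Here IU − W = 20 and the second bracket is 70.

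With v at the control rate, 0.033 × 0.967 = 0.0319, the standard error is 0.0096. Power is Φ(0.027/0.0096 − 1.96) = 0.803. The stated 3090 reproduces, and nothing in this point changes it.

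**3. Scale of the safety comparison.** Fifteen of the 30 site-periods are control, so equal cells give 1,545 patients per phase. At 0.7% this is 1,545 × 0.007 = 10.8 expected events per phase. The 0.7% is a rate for all peri-intubation patients and 1,545 counts enrolled patients, so this is a scale only. The number given an NMB before exclusions is not in the article.

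**4. Power with nothing lost.** Suppose the intervention-phase rate doubled to 1.4% (assumption).
- Two proportions, ignoring site and period: [0.007√1545 − 1.96√(2 × 0.0105 × 0.9895)] / √(0.007 × 0.993 + 0.014 × 0.986) = −0.05, so power is 0.48.
- Stepped wedge as in step 2, with v = 0.0105 × 0.9895 = 0.01039 and the AWP value of ρ borrowed: standard error 0.00548, Φ(0.007/0.00548 − 1.96) = 0.25.

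**5. Power if a share f of the excess falls in excluded patients.** The article gives no f, so the range is an assumption. The rate visible among enrolled patients is 0.7% + (1 − f) × 0.7%.

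| f | Visible rate | Two proportions | Stepped wedge |
|---|---|---|---|
| 0 | 1.40% | 0.48 | 0.25 |
| 25% | 1.23% | 0.32 | 0.17 |
| 50% | 1.05% | 0.18 | 0.10 |
| 75% | 0.88% | 0.08 | 0.06 |
| 100% | 0.70% | 0.025 | 0.025 |

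For a tripling to 2.1%, power is 0.91 and 0.60 with nothing lost, and 0.48 and 0.25 with half lost.

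**6. Effect on the AWP comparison.** Let a share s reach extubation assessable in control and s − δ in intervention, with the extra losses having r times the AWP risk p. The observed rate is (ps − δpr)/(s − δ). With r = 1 there is no shift. With p = 3.3%, s = 0.7, δ = 0.02, r = 2 it is (0.0231 − 0.00132)/0.68 = 3.20%. With s = 0.6, δ = 0.05, r = 2 it is 0.0165/0.55 = 3.0%. All of s, δ and r are assumptions. The largest of these shifts is 0.3 points, against a planned difference of 2.7 points.

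**The case against.** The strongest reply is that the article never restricts the safety denominator to survivors. Table 1 places arrhythmia in the ED column, before the exclusions apply, and nothing says that the ED events of later-excluded patients are discarded. Unexpected events go to the coordinating center as detected. After transition, adverse events are adjudicated centrally and shown to the DSMB, so a fatal arrest could surface that way. A full protocol may also define a safety population.

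Much of this stands. A reader might infer that the trial cannot detect the succinylcholine harm at all. The documents do not support that: the named harm is arrhythmia and not death, non-fatal events remain, and cardiac arrest excludes only with a deficit that prevents assessment. A reader might also subtract an assumed share of fatal events from the 11 expected per phase, but that removes excluded patients from a denominator that already omits them.

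The reply does not remove the point. An ED column says when an event occurs, not for whom it is abstracted, and the only stated rule on who is in the trial is the enrollment rule. The adverse event route gives no by-phase comparison, because adjudication starts only after transition.

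A second tempting reading is that the intention-to-treat statement is false. The article uses the term in the sense of clinician adherence, and patients are analyzed by phase whatever NMB they received. AWP cannot be assessed in a patient who dies intubated, and the title and abstract say survivors. What remains is truncation by death.

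**Conclusion.** The point holds as a defect in how the safety comparison is conditioned. Under the enrollment rule as written, death before extubation and arrest with a disabling deficit leave the enrolled set, so the fatal or disabling form of the named harm would be missed there and mortality would cover only later deaths. This rests on safety being compared in enrolled patients, which the article implies but does not state.

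The loss cannot be sized from the documents. Low event counts are a limit of their own: even with no exclusions, power for a doubling of a 0.7% event is about 0.25 to 0.48. A wider safety set would therefore remove the selection but would not by itself give a decisive test. The absence of adjudicated control-phase events is a separate weakness that adds to this one.

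For the primary outcome, bias needs survival or assessability to differ by phase and to be related to AWP risk. The documents give no evidence of either, and the illustrations above stay small against the planned effect. The sample size is unaffected. This is a worthwhile and cheap improvement to safety reporting. It does not invalidate the primary analysis.

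**What to change.** - Define the safety set as all ventilated adults given an NMB in the ED, in both phases, before the extubation-stage exclusions are applied.
- For this set, abstract from the medical record the Table 1 ED safety events, peri-intubation cardiac arrest (with its timing relative to the NMB, since arrest may also precede it), death before extubation and in-hospital death.
- Report these by phase, together with the number excluded for each reason. Use the site and period model where counts allow. At about 21.6 arrhythmias in all (3090 × 0.007), a model with 11 parameters (intercept, 4 site, 5 period, 1 intervention) has about 2 events per parameter, so counts by site and phase should be tabulated in any case.
- Collect the same events in the same way in the control phase, so that the by-phase comparison does not depend on post-transition adjudication.
- Describe the AWP analysis set as survivors to extubation who can be assessed, analyzed by phase regardless of adherence, and check whether survival and assessability differ by phase.

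The cost is protocol wording and modest extra chart abstraction on screened but excluded patients. The consecutive ventilation alerts already identify them and record review is already planned, so control-phase data may be recoverable. The number of extra charts cannot be derived from the article.
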